## **Randomization 2: Omni-channel PrEP Champion**

We will randomly assign PrEP study participants into two groups. In the intervention group participants will be provided access to the support by an omni-channel PrEP Champion, to help participants adhere to their PrEP routine. Physical support will be provided through group or individual meetings when they come for PrEP refills whereas; virtual support will be via SMS, calls, WhatsApp groups or individual digital conversations. Additionally, clients will receive the national standard of care support, which includes reminders via SMS and phone calls through the health care provider. The PrEP Champions will regularly share informative standardized media including short, Kiswahili animated videos about PrEP use and adherence, essential PrEP messages, pictures, and gifs about PrEP. The media will be developed collaboratively with the National AIDS Control Program (NACP) staff and pre-tested before they are used in the trial. Participants will also be able to ask questions and discuss with and support each other. The WhatsApp messages and physical meetings will be moderated by the trained PrEP Champions. To share the digital information, the PrEP Champions will receive monthly internet bundles from the study team.

In the control group participants will receive the national standard of care, which includes refill reminders via SMS, phone calls and WhatsApp messages as done in the national standard of care. This randomization will be at the individual level. Those who are willing to participate will sign an additional consent form. Participants will be able to drop out at any time and feedback on the utility of the omni-channel PrEP Champions program will be solicited throughout the study. If a participant does not respond to the standard of care reminders and does not show up at her scheduled appointment, the study team will inform the facility or community PrEP lead about the non-responders for further follow up according to the national guidelines.

**Follow up:** We will follow up all PrEP participants every two months for a 6 month period after PrEP initiation to effectively assess retention and safety. We will define loss to follow-up (LTFU) as a participant missing two consecutive follow-up visits with no contact. Efforts will be made to contact LTFU participants (independent from the randomization groups) by phone to understand the reasons for missed visits. If participants are contacted and decide not to return, we will ask them to participate in a

brief exit interview to understand the reasons for dropout and to ensure there are no safety concerns. However, for study participants who will want to continue with the study we will use the approach for intention to treat analysis.

## **4.2 Quantitative Surveys and Qualitative interviews**

Quantitative surveys will be conducted throughout the trial. At baseline, a survey will be conducted with all potential participants and will capture demographic, socioeconomic, work and sexual/reproductive health information. At enrollment a survey will be conducted among eligible participants to assess their motivation to accept or decline the use of PrEP and enrollment in the study. At midline and endline study periods, additional surveys will be employed. Among other things, the survey will inquire about changes to social and sexual practices since initiating PrEP, experienced side effects and self-reported PrEP adherence.

Semi-structured in-depth interviews with a subset of barmaids (n=30) enrolled in the larger trial (N=160) will be conducted at baseline (month 0), midline (month 2) and endline (month 6) to contextualize clinically derived adherence results. These interviews will explore, among other things, understandings of adherence, reasons for non-adherence, challenges to adherence, strategies to improve adherence, and recommendations to improve adherence. Additional questions will explore the barmaid's understanding of PrEP, the drug's mechanism of action, if they perceive the drug as being effective against HIV acquisition, and if this perception (positive or negative) influences their adherence to PrEP. Also, barmaids who have been successfully using PrEP pills for six months and those who have not been involved with PrEP intervention will be invited for interviews on their preferences, willingness to use and factors that may influence uptake of long-acting injectable PrEP. Drawing on the barmaid's personal experience and those of their friends, interviews will also explore trends in PrEP use (drug self-regulation), including times of illness, low perceived risk, sharing of PrEP pills with others etc. During the endline survey, we will also collect information from barmaids, PrEP Champions and health care workers perceptions, their personal understanding and experience on the omni-channel PrEP Champions intervention. Key informant interviews will be conducted with stakeholders like NGOs, health care providers, National AIDS Control Program who are working in HIV

interventions to learn their views on preferences, willingness to provide and feasibility for implementation of long-acting injectable PrEP.

To ensure a meaningful sample is included, a purposive sampling design will be employed. Bar maids will be selected to participate in this qualitative portion in a manner that promotes diverse perspectives and experiences. Therefore, bar maids of varying age, length of employment, marital status, wealth, and other factors established during preliminary fieldwork, will be sought. Additionally, the Barmaids's sexual behavior (recorded at baseline) will be taken into consideration for inclusion into the study. Researchers will work to include barmaids who have only one partner and are in a monogamous relationship, and those in concurrent relationships. Health care workers and other key stakeholders working in HIV will be selected using communication from the municipal social welfare officer and District HIV Coordinator who will help to provide information on stakeholders working in HIV.

Based on the specific objectives of the study, we will use different data analysis softwares to answer them. Therefore, quantitative data will be analysed using the following software; SPSS, Stata, R and SAS depending on the nature of the outcome variables. NVivo [Latest available version] and MAXQDA will be used for qualitative data management and analysis.

### 4.3 Schematic of Study Design

[figure not shown]

---

#### 4.3.1 PRIMARY ENDPOINT

**Initiation on PrEP measured by the proportion of those offered PrEP who are directly observed to initiate PrEP.** The first primary objective of this study is to determine whether offering immediate, on-site PrEP initiation raises initiation rates relative to a peer-navigator led, facility-based initiation process. This endpoint will measure whether the workplace-based initiation process improves uptake, and thus improves the ability of PrEP programs to protect those at high risk of HIV acquisition.

**Adherence to PrEP measured by urine drug level at 6 months post-enrollment.** The second primary objective of this study is to determine PrEP initiation and drug refill at women's workplaces will improve adherence to PrEP treatment. Measuring adherence to PrEP using urine drug level is the most precise and direct way to measure adherence in the recent past, and thus whether the participant is currently using the drug. Self-report of PrEP use is likely to be biased by social desirability. Ongoing adherence to PrEP is vital to maintaining the protective effect of ART against HIV infection. The primary endpoint will be measured across the two delivery method groups: facility-based and workplace-based PrEP delivery. Women who default from PrEP treatment or are lost to follow up will be assumed to have zero TDF in their urine.

**Thesis;** this will be a qualitative study that will document Barmaids' preferences, willingness to use, factors influencing uptake of long-acting injectable HIV PrEP and feasibility of implementing injectable PrEP.

---

#### 4.3.2 SECONDARY ENDPOINTS

**Retention in PrEP care measured by refill rates at each study visit;** This secondary endpoint will be analyzed in two ways: first, comparing the omni-channel PrEP Champion intervention to no omni-channel PrEP Champion intervention to evaluate secondary objective 1; and second to compare facility- and workplace-based PrEP delivery groups as a supporting analysis for the primary objective. Retention in care reflects the proportion of those initiating care who remain accessible to programs, and thus potentially able to take PrEP.

**Documentation of the performance of a point of care urine assay as a measure of adherence to PrEP**; will be carried out qualitatively. Health providers will be asked about their experience with the test, including ease of use and interpretation. Additionally, the interpretation of the test onsite will be compared with those conducted by the test’s designers as quality control to assess the extent to which they align.

---

### **4.3.3 EXPLORATORY ENDPOINTS**

1. Level of HIV-related knowledge, including PrEP
2. Characteristics of those accepting and declining to initiate PrEP
3. Proportion of those initiating PrEP retained in care at each study visit
4. Proportion of those initiating PrEP reporting >85% adherence at each study visit
5. Proportion of those initiating PrEP reporting side-effects
6. Number of HIV seroconversions at each study visit
7. Change in number of sexual partners reported in past 30 days from initiation to each study visit
8. Proportion of women reporting consistent condom use at baseline and final visit
9. Proportion of those initiating PrEP with STI symptoms at each study visit
10. Proportion of those initiating PrEP receiving a routine follow-up.
11. Proportion of those initiating PrEP declining being part of the omni-channel PrEP Champions intervention at baseline and at each study visit.
12. Proportion of those initiating PrEP with Tenofovir urine levels compatible with weekly dosing, dosing in the past 2 to 3 days, and dosing within the past 24 hours.

## **5. STUDY ENROLLMENT AND WITHDRAWAL**

### **5.1 Participant Inclusion Criteria**

Individuals must meet all of the following criteria in order to be eligible to participate in this study:

- Identify as female and report being aged 15 years or older

- Working in a licensed bar in Ubungo Municipality Dar es Salaam Municipality(DSM) as a barmaid or server
- Provide signed and dated written informed consent
- State that they are willing to comply with all study procedures and available within DSM for the duration of the study
- Be able to take oral medication and be willing to adhere to the medication regime
- Ability to consent
- A working experience of at least 2 months
- Barmaids who have used PrEP pills consistently for six months and those who have not used PrEP will be recruited for qualitative interviews on long-acting injectable PrEP

## **5.2 Participant Exclusion Criteria**

- Report past diagnosis of renal disease
- Report past diagnosis of diabetes
- Report past diagnosis of hypertension
- Report current use of nephrotoxic medication
- Report flu-like symptoms that may represent acute HIV infection
- Report currently taking any of the following medications:
  - Any medicine containing emtricitabine or tenofovir disoproxil fumarate
  - Any medicine containing tenofovir alafenamide
  - Any medicine containing lamivudine
  - Adefovir
  - Didanosine
  - Atazanavir
  - Ledipasvir with sofosbuvir
  - Darunavir
  - Lopinavir with ritonavir
- Report bone pain or other bone problems
- Test positive for HIV or be unwilling to complete HIV counselling and testing.
- Test abnormally low for renal function using a serum creatinine test (<60ml/min).

- Test positive for Hepatitis B based on a hepatitis B surface antigen (HBsAg) test.

### **5.3 Strategies for Recruitment and Retention**

The study aims to recruit 160 HIV negative barmaids to initiate the PrEP intervention. We expect to screen 1204 barmaids in order to recruit these 160 women. There will be only one study site in Dar es Salaam and all individuals will be recruited in Tanzania by locally employed staff.

Participant recruitment will be carried out by visiting licensed bars in DSM, after an initial telephone conversation with the license-holder or representative. On arrival at the bar, the study team will work with the on-duty manager to make a list of all women working as barmaids providing drinks directly to customers. The bar manager will be given a small payment for the time taken to complete the listing and for the inconvenience of the study team's presence. Every woman on this list will then be invited to participate in a screening process including a questionnaire and HIV counselling and testing (HTC). Barmaids will be interviewed in within private tinted mobile vehicles or in a conducive and private place which will be proposed by the barmaids in order to maintain confidentiality. At the initial recruitment stage, potential participants will be offered a small gift (~US\$3) to compensate them for the time spent away from their work while completing screening activities. This will be provided at the end of the screening process, unconditional on study inclusion. Approval and support for the study will be obtained from the District Medical Officer of each district in Dar es Salaam where the study will be conducted.

No vulnerable individuals will be targeted for recruitment.

### **5.4 Participant Withdrawal or termination**

#### **5.4.1 Reasons for Withdrawal or Termination**

Participants are free to withdraw from participation in the study at any time upon their requests and on their will without being forced or intimidated. The participants will be given clear explanation on the study, process and all procedures that will be done. The issue of withdrawal will be explained clearly that they can stop to participate in the study at any time and that their

withdrawal from the study will have no influence on how they will be treated or handled afterwards.

An investigator may terminate participation in the study (i.e. stop provision of PrEP) if:

- A participant tests positive for HIV
- A participants' renal function drops abnormally low
- Any clinical adverse event (AE), laboratory abnormality, or other medical condition or situation occurs such that continued participation in the study would not be in the best interest of a participant
- A participant ceases to work as a barmaid in Dar es Salaam

Apart from the above reasons for withdrawal or termination of participation in the study, the informed consent has a component that explains about stopping participation and that it will not impose any penalty to the participant.

---

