### **Randomization 1: PrEP delivery method**

We will randomly assign bars to one of two PrEP delivery groups: facility-based or workplace-based. All women enrolled onto PrEP from each bar will be assigned to their bars' study group, i.e. this is a cluster-randomized design. Bar-level clusters will be used to avoid study contamination and ensure smooth study operationalization.

**Group 1a. Facility-based PrEP delivery:** All HIV-negative participants in facility-based group bars will be offered the opportunity to initiate PrEP. If they agree to participate, they will be introduced to an assigned peer navigator. The peer navigator will arrange a time to escort the barmaid to their preferred health facility (from the list prepared by the study team) for PrEP services. At the facility, they will be started on emtricitabine/tenofovir disoproxil, with direct observation of the first dose. The study team will actively follow-up the clients to discontinue the participant from PrEP in case they show any signs of side effects. This practice of immediate initiation of treatment followed by discontinuation of treatment among participants with contraindications is comparable to Tanzanian's current guidelines for immediate initiation of ART in HIV-positive patients and PrEP implementation framework.

At the enrolment visit, participants will be scheduled for regular follow-up visits at the facility to monitor medication adherence and safety, once every 2 months, and to receive a PrEP prescription refill on monthly basis.. These visits will include HIV testing, creatinine levels, screening and treatment for STIs as required, and adherence counselling. All these services are standard of care for monitoring patients on treatment and fulfill monitoring requirements in national PrEP and HIV treatment guidelines [24].

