**Group 1b. Workplace-based PrEP delivery:** HIV-negative participants in workplace-based group bars will be offered the opportunity to initiate PrEP at the bar immediately. If they agree to participate, they will be started on emtricitabine/tenofovir disoproxil, with direct observation of the first dose. This initiation will be conducted by study healthcare staff who are allowed to prescribe ART as per Tanzania national policy. Again, should test results subsequently show that participants meet for side effects or other exclusion criteria, the study team will actively follow up to discontinue the participant from PrEP. All subsequent visits will be as in the facility-based group but carried out at the workplace with the assistance of the Community based HIV care providers. The Community based HIV care providers will provide refills; conduct monitoring,

and record inconveniences encountered – since this is an important part of the feasibility assessment for this mode of delivery.

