#### **5.4.2 Handling of Participant Withdrawals or termination**

Participants who discontinue PrEP, but otherwise will remain eligible for the study, will remain eligible for follow-up visits at their healthcare facility or bar workplace. Study team members will continue to reach out to these individuals by phone to invite them to scheduled follow-up visits – in order to capture any adverse events or unanticipated problems. Withdrawn or discontinued participants will not be replaced, since such events represent a meaningful endpoint for analysis.

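### Sections 5.4.1 and 5.4.2 leave some women stopped on PrEP without assured safety visits, although section 4.1 promises six months of follow-up to all

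*Protocol*

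**What the plan says.** The follow-up paragraph of section 4.1 attaches no eligibility condition: "We will follow up all PrEP participants every two months for a 6 month period after PrEP initiation to effectively assess retention and safety".

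Section 5.4.1 begins "An investigator may terminate participation in the study (i.e. stop provision of PrEP) if" and gives four reasons: a positive HIV test; abnormally low renal function; an adverse event, laboratory abnormality or other condition that makes continuing against her interest; and no longer working as a barmaid in the city.

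Section 5.4.2 says who keeps visits: "Participants who discontinue PrEP, but otherwise will remain eligible for the study, will remain eligible for follow-up visits". Phone invitations go to that same group. The stated purpose is to pick up adverse events and unanticipated problems.

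Section 5.2 excludes women who "Test positive for HIV or be unwilling to complete HIV counselling and testing", as well as those with renal function below 60 ml/min or a positive HBsAg test. Section 5.1 requires work in a licensed bar in the municipality.

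Section 4.1 foresees stops soon after the first dose in both arms. For the workplace arm it says "should test results subsequently show that participants meet for side effects or other exclusion criteria, the study team will actively follow up to discontinue". For the facility arm it refers to "This practice of immediate initiation of treatment followed by discontinuation of treatment among participants with contraindications".

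**The concern.** Section 4.1 gives safety follow-up to all women who start PrEP, while 5.4.2 makes it conditional. Some of the women who fail the condition are those whose later course is of safety interest. Section 2.4.1 names hepatitis B exacerbation and renal impairment as possible adverse reactions to the drug, and both correspond to exclusion criteria.

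If stopping PrEP also ends participation, section 8.3 starts a clock: new events are recorded for only 7 more days (30 for serious events). Section 8.5 halts the study for review at four serious events, or at two judged likely to be related to study procedures. With thresholds this low, even one uncaptured serious event could matter.

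**Working it through.** The protocol gives no figure on this point, so the check is mainly a comparison of texts.

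**Who fails the condition in 5.4.2**

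- *Positive HIV test, low renal function.* Both are stop reasons in 5.4.1 and exclusions in 5.2 (5.4.1 itself gives no 60 ml/min threshold). These are two of the four stop reasons.
- *Left bar work.* This is a stop reason in 5.4.1 and fails an inclusion criterion in 5.1.
- *Adverse event or other condition.* Where this matches no 5.2 criterion, she remains otherwise eligible and keeps her visits.
- *Late baseline result.* This is not listed in 5.4.1 but follows from 4.1. Creatinine is a laboratory test, so a result after the first dose is plausible. HBsAg enters only by this route, and only if it is sent to the laboratory as in 7.2; section 7.3.1 describes it as point-of-care.

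**What each reading of the condition does**

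- If *otherwise* means apart from having stopped PrEP, a woman who is now HIV-positive still fails, because HIV status is a separate criterion.
- If it means apart from the reason for stopping, she passes. The condition then removes almost nobody.

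**Illustration only, on the reading that participation ends at the stop**

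A completer's recording ends at Day 180 + 7 = 187 (AE) and 180 + 30 = 210 (SAE). For a stop on Day s it ends at s + 7 and s + 30, which is 180 − s days earlier in both cases. The schedule in 7.3.6 places adverse event evaluations at Visits 1 to 6 (Days 30, 60, 90, 120, 150 and 180).

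| Stop day | Basis | AE / SAE recording closes | Days earlier | Evaluations lost (net of one early termination visit) |
|---|---|---|---|---|
| 1–14 | Late baseline result; turnaround assumed | 8–21 / 31–44 | 166–179 | 6 (5) |
| 30 | HIV test, Visit 1 | 37 / 60 | 150 | 5 (4) |
| 60 | Creatinine, only if done at two-monthly visits | 67 / 90 | 120 | 4 (3) |
| 120 | HIV test, Visit 4 | 127 / 150 | 60 | 2 (1) |
| 180 | Month 6 tests | 187 / 210 | 0 | 0 (0) |

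The Day 60 row depends on section 4.1, which says of the regular visits "These visits will include HIV testing, creatinine levels, screening and treatment for STIs as required, and adherence counselling". The schedule has creatinine only at screening and month 6, and on that schedule renal decline costs no days.

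If a woman off PrEP would attend only Visits 2, 4 and 6, the gross losses for the first four rows are 3, 3, 2 and 1. An early termination visit 0–14 days after the stop (assumed) would move the closing dates by the same amount; the Day 30 case becomes 136–150 days.

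**Number of women**

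The protocol gives no HIV incidence. Assuming 1–5 infections per 100 person-years, 160 women over 120 days contribute 160 × 120/365 = 52.6 person-years. That gives 52.6 × 0.01 = 0.5 to 52.6 × 0.05 = 2.6 women. The protocol offers no basis for counting laboratory stops or departures from bar work.

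**The case against.** The strongest reply is that section 5.2 is an entry list. It also excludes women currently taking emtricitabine or tenofovir disoproxil fumarate, so applying it during follow-up would disqualify everyone on study drug. The schedule marks eligibility only at screening and baseline, and 7.3.2 verifies criteria at Visit 0. On this view the parenthesis in 5.4.1 narrows termination to stopping the drug, and 5.4.2 keeps visits open for the purpose it states, in agreement with 4.1.

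This shows that a benign reading is available, but it does not remove the problem. Section 5.4.2 itself applies study eligibility after enrolment, and only to women already off PrEP, so the drug criterion causes no absurdity there. The third reason in 5.4.1 speaks of participation as such, and 7.3.5 provides an early termination visit. The protocol therefore does expect some participation to end early.

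Other parts of the reply stand. Clinical care is not lost: sections 4.1 and 11.4.2 provide linkage to HIV treatment and referral, with transport funds, for other diagnoses, and 2.4.1 sends HBsAg-positive women to specialised clinics. Section 8.3 follows open events to resolution and allows events to surface when a woman presents for care.

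A reader might infer that every woman stopped for safety loses follow-up, or that a positive HBsAg test is a listed stop reason. The text supports neither. Only stops that coincide with an eligibility criterion are at issue, and HBsAg is not in the 5.4.1 list.

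**Conclusion.** The point holds as a minor one. The natural reading of 5.4.1 and 5.4.2 falls short of the promise in 4.1 for the groups identified above. The text does not require that reading, so it cannot be said that the protocol drops these women.

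The loss is limited to trial recording of new adverse events after the stop, and to the month 6 tests if no early termination visit takes place. The day counts illustrate one of two readings, partly on assumed timings, and are not an estimate of harm. For HIV, the assumed incidence range gives fewer than three women.

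It would be wrong to infer bias in the main comparisons. Primary endpoint 1 is settled at the first dose. For primary endpoint 2, sections 9.4.1 and 10.5.2 assign zero TDF to women who discontinue, default or are lost.

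**What to change.** In 5.4.1, delete the reference to ending participation, so that the sentence says only that the investigator may stop provision of PrEP for the listed reasons.

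In 5.4.2, replace the eligibility clause with: *Every woman who took a first dose and stops PrEP for any reason is invited to the remaining scheduled follow-up visits (or contacted by phone) to month 6, unless she withdraws consent or the investigator judges that further contact is against her interest.*

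Merely adding that eligibility is judged apart from the reason for stopping would mend 5.4.2. It would still leave 5.4.1 equating the two acts, and so leave unclear when the recording window in 8.3 starts.

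The cost is two wording changes and a few extra visits or calls. The visits are already scheduled and 5.4.2 already provides for phone outreach, which also serves women who have left the bar.
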